Across the literature, four key knowledge gaps persist: (1) we generally know little about the characteristics of day program attendees and nonattendees, or about those with different patterns of use. (2) We lack longitudinal data on changes in the aforementioned outcomes. (3) Generally, the methodological quality of available studies is poor [32], and we lack robust, large-scale, longitudinal evidence of older adult day programs on day program attendees—especially those living with dementia. With few notable exceptions [42,43], we especially lack current research on Canadian day programs with most research originating from the US or Canadian studies often dating back several decades [25,26,44]. (4) Differential effects of day programs on persons with multiple, intersecting vulnerabilities are poorly understood, despite inequity concerns [39,45-47]. Advanced age puts individuals at risk of ageism; physical and cognitive disabilities may expose them to ableism; the majority of older adults and their caregivers are women, often experiencing gender inequities; and giving and receiving care are associated with substantial health care costs, disproportionally affecting those with low income [48]. Racism or transphobia or homophobia can further increase these pressures, severely affecting older adults and their caregivers [49,50].

Our study will address these knowledge gaps comprehensively, rigorously, and simultaneously. We will address the following 3 research objectives:

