#### Study Outcomes

The data sources noted above enable us to examine a range of important study outcomes. Data on the time between a person’s first RAI-HC assessment and admission to a care home will come from provincial continuing care registries. Symptoms of depression will be assessed using the validated RAI-HC Depression Rating Scale [72], with scores ranging from 0 to 14 and a cut point of 3 or higher representing clinically meaningful depressive symptoms [72,73]. We will capture physical and cognitive decline, using validated RAI-HC scales [64]: the Activities of Daily Living Hierarchy (ADLh) Scale [74] and the Cognitive Performance Scale (CPS) [75]. Both scales range from 0 (no impairment) to 6 (maximum impairment), and our outcomes will be dichotomous, indicating any increase (vs no change or a decrease) between the previous and follow-up measurement in each of these scales. Using care practitioner claims data, we will generate rates of different types of primary and specialist care use (eg, family physician, specialists, nursing practitioner, and allied health providers). We will use the DAD and NACRS databases to generate rates of emergency department registrations, hospital admissions, and days in hospital (including alternative level of care) [43]. Rates will be stratified by day program use or nonuse pattern.

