#### Propensity Score–Matching Variables

To compare outcomes between day program attendees and nonattendees, we will use propensity score matching [78] (for details, see Statistical Analyses section). Propensity scores aim to ensure a similar distribution of baseline variables among treatment (day program attendees) and control (nonattendees)—akin to what random assignment aims to accomplish in randomized trials [78]. Since we lack evidence on differences between day program attendees and nonattendees, our objective 2 analyses will be key to informing the selection of the exact covariates that will form the propensity score. We will derive covariates for day program attendees from the RAI-HC day program eligibility assessment (index date). For each day program attendee, we will identify potential matches as nonattendees whose first RAI-HC assessment was completed within ±3 months of the attendee’s index date (ie, admission to long-term home care at about the same time). This RAI-HC assessment will provide the relevant covariates to enable propensity score matching with day program attendees as of their index date.

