Our first set of matching covariates will be RAI-HC variables used by health systems to determine day program eligibility [60,65,66]: physical functioning (ADLh Scale), cognition (CPS), behavioral symptoms (Aggressive Behavior Scale [79]), bladder or bowel continence (items I1, I3), availability of a caregiver (item G1e), and caregiver distress (items G2a-c). This will ensure that control participants are potentially eligible to a day program. Possible reasons for nonattendance include the lack of day program spaces, preference not to attend, inability to afford the required copayments, or not receiving a day program referral. Our experts assure us that the pool of potential matches far exceeds that of attendees, supporting the feasibility of this study and underscoring the lack of day program spaces. This approach excludes individuals whose care needs are either too low or too severe for day program eligibility, but it minimizes confounding by the matched variables and ensures comparable groups at baseline [80-82]. Finally, we will include a second set of matching covariates: health and social characteristics identified in objective 2 by which attendees and potentially eligible nonattendees differ and that overlap sufficiently between attendees and nonattendees (eg, age, sex, type or duration of publicly funded community care received before the matching index date, and deprivation indices).

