#### Objective 2: Compare Older Adults’ Characteristics by Day Program Use, Province, and Time

Using our full cohort of day program attendees and nonattendees, we will descriptively assess the distribution of sample characteristics over time and by province. In each province and quarter, we will report and plot graphically the proportion (95% CI) of individuals with each characteristic, stratified by day program use class versus nonuse. Using general estimating equations (GEEs) [83], we will assess whether the number of persons with each characteristic has changed over time and whether characteristics are associated with older adults’ day program use or nonuse pattern. We will run a separate GEE model for each characteristic within each province, with the respective characteristic as individual-level outcome. We will run binary logistic regressions for dichotomous variables (eg, sex) and ordinal regressions for categorical variables (eg, residential instability quintile). Models will account for repeated measures within individuals and include the independent variables year of assessment (to assess change in social determinants over time), use or nonuse class (to assess differences in social determinants by day program use), and an interaction between year and use or nonuse (to assess how social determinants differed between use and nonuse patterns by year). Using random-effects mixed regression models, we will pool provincial effects statistically. Other Pan-Canadian studies, such as the Canadian Network for Observational Drug Effect Studies [84], have successfully applied this approach and developed rigorous protocols to minimize bias and maximize consistency of regional analyses.

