Using GEEs and a similar approach as for the time-to-event models (including separate models in each province and statistical pooling of their effects), we will assess whether the other study outcomes differ by day program use or nonuse pattern. Models will include each study outcome of interest as a dependent variable, day program use or nonuse class and time of assessment as independent variables, and similar covariates (using the same stepwise approach) as the time-to-event models. Models will also include a random term to account for repeated measures within individuals. The choice of a link function will be informed by the nature of the variable and theoretical and empirical considerations. For example, the number of hospital, emergency department, or physician visits has been shown to follow a zero-inflated negative binomial distribution, sometimes requiring an offset for the natural logarithm of person-time [92]. For continuous outcomes (eg, days spent in hospitals), we will use an identity link function, and for dichotomous outcomes (eg, presence or absence of depressive symptoms), we will use a logit link function. All models will apply multiple imputation in case of missing data, which we expect to be small based on our previous work with the administrative health care data sources used in this study.

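### The depressive-symptom GEE in objective 3 names neither the index depression score nor which assessments count as outcomes, so its class coefficient is a level difference that carries any imbalance at index

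*Protocol article*

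**What the plan says.** The section on objective 3 gives the GEEs for outcomes other than care home admission these terms: "day program use or nonuse class and time of assessment as independent variables". Covariates are added by the same stepwise approach as in the time-to-event models, and a further term handles repeated measures within a person. No product of class and time is named. The objective 2 GEEs, by contrast, name "an interaction between year and use or nonuse".

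Depressive symptoms are defined under Study Outcomes by the DRS, with "a cut point of 3 or higher representing clinically meaningful depressive symptoms". The objective 3 text confirms that the analysed variable is a status: "for dichotomous outcomes (eg, presence or absence of depressive symptoms), we will use a logit link function". Physical and cognitive decline (ADLh, CPS) are defined differently, as a binary variable "indicating any increase (vs no change or a decrease) between the previous and follow-up measurement".

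The baseline is fixed under Propensity Score–Matching Variables: "We will derive covariates for day program attendees from the RAI-HC day program eligibility assessment (index date". For nonattendees it is the first RAI-HC within 3 months either side of that date. The eligibility-based matching set begins "physical functioning (ADLh Scale), cognition (CPS), behavioral symptoms (Aggressive Behavior Scale" and goes on to continence and caregiver items. DRS is not named in it. A second set, chosen from the objective 2 results, is left open.

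**The concern.** With a repeated status outcome and main effects for class and time only, the class coefficient is one log odds ratio, assumed constant over all assessments in the data set. It answers whether the groups differ on average. It does not answer whether they diverge after attendance begins unless the index level is dealt with, by adjustment or by a contrast with index.

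Two things follow for depression. First, if the matched groups differ in DRS at index, that difference is part of the coefficient. Nothing prespecified removes it, because DRS is neither a named matching variable nor a named covariate. Second, if the index assessment is itself an outcome row, a contrast on which the program cannot yet have acted is averaged into the effect.

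This matters because the Introduction names the gap the study is meant to fill: "We lack longitudinal data on changes in the aforementioned outcomes". The large expected sample does not help, since neither problem shrinks as numbers grow.

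**Working it through.** The article gives no figure for the GEE outcomes, so there is none to reproduce. Its total of 1327 concerns the Cox model for care home admission and has no bearing here.

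**Inputs.** From the article: the model terms, the DRS cut point of 3 or higher, the index assessment and the named matching variables. Also from the article, under Sample Size Calculation: about 50% of those assessed are reassessed within 12 months and another 10%-30% after more than 15 months, so many people will contribute few follow-ups. Assumed, for illustration only: the odds ratios below.

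**Formula.** Let d be the log odds ratio (attendee versus nonattendee) at index, and d + c the log odds ratio at each of k follow-ups, so that c is the change. With time as a factor and roughly equal weight per assessment, the class coefficient is close to the mean of the time-specific log odds ratios:

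- index row kept: d + c × k/(k+1)
- index row left out, no index adjustment: d + c

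**Case A: index row kept, groups equal at index (d = 0).** The coefficient is the follow-up odds ratio raised to the power k/(k+1).

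| Follow-ups k | Share of log OR kept | Follow-up OR 0.79 | Follow-up OR 0.70 |
|---|---|---|---|
| 1 | 1/2 | 0.889 | 0.837 |
| 2 | 2/3 | 0.855 | 0.788 |
| 3 | 3/4 | 0.838 | 0.765 |

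Two simulations agree. A pooled logistic model on 2 million people (random-intercept SD 1.2, marginal follow-up OR 0.79) gave 0.891, 0.855 and 0.839. An exchangeable logit GEE with 12,000 per group (25% prevalence, random-intercept SD 1.5, follow-up OR 0.70) gave 0.83, 0.79 and 0.75. With the index row dropped, the second gave 0.67, 0.71 and 0.68, which is 0.70 within simulation error.

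**Case B: groups unequal at index.** Take a change odds ratio of 0.70 and k = 2.

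| Index OR | Index row kept | Follow-ups only, unadjusted |
|---|---|---|
| 0.80 | 0.80 × 0.788 = 0.63 | 0.80 × 0.70 = 0.56 |
| 1.25 | 1.25 × 0.788 = 0.99 | 1.25 × 0.70 = 0.875 |

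The simulated GEE with the index row kept gave 0.64 and 1.04. These are single data sets, so small departures from the formula are expected. Against 0.70, the coefficient is exaggerated in the first line and attenuated or abolished in the second. Dropping the index row alone does not cure this. The index value has to be in the model.

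**Case C: index row left out, groups equal at index, effect growing.** With odds ratios of 0.96, 0.84 and 0.71 in years 1 to 3, equal weights give (0.96 × 0.84 × 0.71)^(1/3) = 0.83. Weights of 70/20/10% give exp(0.7 ln 0.96 + 0.2 ln 0.84 + 0.1 ln 0.71) = 0.91. Both are correct averages with different weights, so neither is biased for its own target. The single figure just does not show the trend.

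**The case against.** The strongest reply is that the article never says the index assessment is an outcome row. Its only stated role is to set the index date and supply matching covariates, and a condensed article may leave the analysis data set to a fuller plan. This stands. A reader might infer that the planned estimate is biased toward no effect, but the text does not support that: the dilution is conditional on the row being kept, and its direction further requires equal DRS at index.

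The list of model terms may also be incomplete. The objectives promise effect modification by class, age, sex and social determinants, yet the objective 3 analysis text names no interactions. The absence of class by time is therefore not proof of a decision against it. The objective 2 interaction uses calendar year of assessment for a descriptive question, so it is only a weak comparator. These points stand too, and so does the point that a post-index average odds ratio is a legitimate target.

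Outcomes are also to be compared in every year and province. Those are bivariate tests without adjustment for the index score, so they do not replace a model-based contrast.

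Finally, DRS could still enter through the second matching set or the stepwise selection (P of .15 or less in bivariate analyses). That is possible but not assured, and an outcome's own baseline should not depend on a screening P value.

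**Conclusion.** The point holds for depressive symptoms in a limited form. The objective 3 GEE, as written, estimates a level difference with no prespecified adjustment for index DRS, so any index imbalance passes into the class coefficient in full and in either direction. If the index row is also kept and the groups are equal at index, about one half, one third or one quarter of the log odds ratio is lost with one, two or three follow-ups. The sizes rest on assumed odds ratios, roughly equal weight per assessment and a constant follow-up effect in Cases A and B. The article supplies none of these.

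Two wider readings are not supported. Leaving out class by time does not make a post-index average odds ratio biased. It leaves the course of the effect undescribed. And the index-row argument does not reach ADLh or CPS decline, which are scored as worsening since the previous measurement, so the index assessment supplies the starting value and is not an outcome. This is an inexpensive improvement to the specification, not an error that invalidates the analysis.

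**What to change.** In the objective 3 GEE text, for depressive symptoms:

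1. State that only assessments after the index date are outcome rows.
2. Include the index DRS as a prespecified covariate, outside the stepwise selection.
3. Define the time variable as time since the index date, for attendees and their matched nonattendees alike.
4. As a secondary analysis, add class × time, or the simpler attendance × time, and report contrasts at fixed times since index.

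Items 1 to 3 need wording only, as the index DRS is already collected in the RAI-HC. The resulting odds ratio is conditional on index DRS and should be described so. People with no reassessment contribute no depression outcome, which should be reported. Item 4 costs more: with several latent classes plus nonuse, fitted separately in three provinces, the parameters multiply and time-specific intervals widen. Attendance × time keeps that cost down.

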### Sample Size Calculation

The yearly average number of completed RAI-HC assessments is ~20,000-30,000 in Alberta, ~34,000-39,000 in British Columbia, and ~10,000 in Manitoba [67]. About 50% of those assessed receive a reassessment within 12 months and another 10%-30% receive a reassessment after >15 months [68]. There are 89 publicly subsidized day programs in Alberta (~3300 spaces per day), 95 in British Columbia (~1500 spaces per day), and 70 in Manitoba (~1000 spaces per day) for a total of 254-day programs with 5800 spaces on any given day. Some day program users do not attend daily, but only 1 or a few days per week, so the number of unique attendees exceeds the number of spaces per day. This corresponds to >20,000 attendees per year (>200,000 within the study period), each with multiple assessments. Our study sample size will be large enough to detect small effects sizes. With Cox proportional hazards models, adjusted for covariates explaining an assumed 25% of effect variance (a=.05; power=0.8) [69], we require a total sample of 1327 participants to detect a hazard ratio for admissions to care homes of 0.6 (as can be expected based on a similar Canadian study [42]) in favor of day program attendees. Similarly, Kelly [43] was able to detect significantly fewer emergency department visits and hospital admissions per day among 812 day program attendees compared with 812 propensity score matched to nonattendees. Our expected sample size will be considerably larger than for those previous studies, allowing for complex statistical modeling.

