### Data Sources

For each individual in our cohort, designated provincial health system analysts will link all records available within the study time frame from the following databases: (1) regional continuing care registries, documenting when an individual starts or stops receiving any community-based continuing care, including day programs, how these services change over time, and when an individual is admitted to a care home. (2) Population registries for each participant’s demographic data. (3) RAI-HC assessments [64], completed annually for people receiving long-term home care (60+ days), and to determine day program eligibility. The RAI-HC will provide data on older adults’ medical conditions, functional dependence, pain, cognitive impairment, mood, and behavioral problems. It also includes information on a person’s marital or partnership status, caregiver availability, whether that caregiver lives with the older adult, and caregiver distress. Additional caregiver characteristics are not included in the available provincial databases, posing a limitation to our quantitative analyses. However, a related prospective cohort study that we are conducting in Ontario will allow us to link comprehensive caregiver and older adult data, and we are currently conducting additional qualitative research that will illuminate how caregiver characteristics may affect day program use and outcomes. (4) Discharge abstract database (DAD) for information on all inpatient hospital stays, including diagnoses and length of stay. (5) National Ambulatory Care Report System (NACRS) for all emergency department visits and diagnoses. In British Columbia, we will use the physician payment file in addition, since NACRS is not collected in all emergency departments [70]. (6) Pharmaceutical information on outpatient prescription medications filled through a community pharmacy and covered by provincial drug formulary. (7) Care provider claims data for health service claims submitted for payment by health care providers (eg, general practitioners, nurse practitioners, geriatricians, geriatric psychiatrists, neurologists, therapists) to obtain information on general and specialist health services used by participants.

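### ADLh and CPS decline is counted between consecutive assessments without accounting for the time between them, although the plan's own figures show that this time varies

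*Protocol article*

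**What the plan says.** All passages are in the protocol article.

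- **Outcome (Study Outcomes).** For the ADLh Scale and the CPS, "our outcomes will be dichotomous, indicating any increase (vs no change or a decrease) between the previous and follow-up measurement in each of these scales". No interval length, rate or assessment window is attached.
- **Model (Statistical Analyses, Objective 3).** The non-survival outcomes are analysed by GEE, with a logit link for dichotomous outcomes. Time of assessment is a covariate, but its origin is not defined. An offset for person-time is mentioned only for counts of visits.
- **Assessment frequency (Sample Size Calculation).** "About 50% of those assessed receive a reassessment within 12 months and another 10%-30% receive a reassessment after >15 months".
- **What triggers an assessment (Data Sources).** The RAI-HC is "completed annually for people receiving long-term home care (60+ days), and to determine day program eligibility".
- **Index assessments (Propensity Score–Matching Variables).** For attendees, the index is the assessment that established eligibility for a day program. Controls are "nonattendees whose first RAI-HC assessment was completed within ±3 months" of that date.
- **Missing data (Statistical Analyses, Objective 3).** "All models will apply multiple imputation in case of missing data, which we expect to be small", an expectation based on earlier work with these data sources.
- **End of follow-up (Setting and Sample).** Follow-up stops at care home admission, death or other loss, or at the end of 2024.

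**The concern.** An outcome that records whether a score rose since the last measurement is a cumulative risk over the gap between measurements. When gaps vary, the same underlying rate of decline gives different proportions with decline. A logit model without the gap then mixes rate of decline with spacing of assessments.

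This would only add noise if spacing were unrelated to exposure. The documents give reason to doubt that. One trigger for an RAI-HC is the exposure pathway itself, and the two groups start from different kinds of assessment: an eligibility assessment for attendees, the first RAI-HC for nonattendees. An eligibility assessment done between two annual ones, for instance, would shorten the gaps around it. Matching on baseline covariates does not equalise later spacing. Less physical and cognitive decline is a named aim of objective 3, so an artefact here could be read as a program effect. The plan expects more than 200,000 attendees, so sampling error would give little protection against even a modest bias.

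**Working it through.** The plan computes no figure for the decline outcomes. Its one calculated size, 1327, concerns care home admission and plays no part here.

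**Step 1. What the reassessment figures imply.**
- Within 12 months: about 50%. After more than 15 months: a further 10% to 30%.
- In either stated window: 50% + 10% = 60%, up to 50% + 30% = 80%.
- In neither: 100% − 80% = 20%, up to 100% − 60% = 40%. These people were reassessed at 12 to 15 months or never; the text does not separate the two.
- Among those in the two windows, the share within 12 months is 50/60 = 83% or 50/80 = 62.5%.

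The gaps therefore vary materially.

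**Step 2. Effect of the gap on the outcome, with no true effect.** Assume a constant decline hazard h, the same in both groups, so that P(t) = 1 − exp(−ht) and the odds are exp(ht) − 1. With h = 0.3 per year (an assumption, not in the documents):

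| Gap | P(any increase) | Odds |
|---|---|---|
| 12 months | 1 − exp(−0.300) = 25.9% | 0.350 |
| 15 months | 1 − exp(−0.375) = 31.3% | 0.455 |
| 18 months | 1 − exp(−0.450) = 36.2% | 0.568 |

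- One group at 12 months, the other at 15: OR = 0.350/0.455 = 0.77.
- One group at 12 months, the other at 18: OR = 0.350/0.568 = 0.62.
- For h from 0.2 to 0.4 per year, these ORs run from 0.78 to 0.76 and from 0.63 to 0.60.

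**Step 3. A milder imbalance.** Let 83% of one group's reassessments fall at 12 months and 62.5% of the other's, with the rest at 18 months. This borrows the two ends of the range in Step 1 as if they were the two groups, for illustration only.
- 0.83 × 25.9% + 0.17 × 36.2% = 27.7%
- 0.625 × 25.9% + 0.375 × 36.2% = 29.8%
- OR = (0.277/0.723)/(0.298/0.702) = about 0.90

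With equal mixes in the two groups the OR is 1.

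**Step 4. Whether the remedy removes it.** Under the same assumption, log(−log(1 − P)) = log h + log t. With log t as an offset and a complementary log-log link, the group coefficient estimates the log hazard ratio, which is 0 here whatever the gaps.

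**The case against.** The strongest reply is that time is already in the model. If time of assessment is counted from the index date, it equals the gap at the first follow-up and would absorb much of the problem there; its coding could be left to an analysis plan. This stands in part. At later assessments time since index is not the gap, and if the term means calendar time it never is. The article itself fixes the outcome definition and the logit link, and it mentions a person-time offset only for counts, so this is a stated choice and not just an omitted detail.

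The illustration can also be attacked. An OR of 0.62 needs all of one group at 12 months and all of the other at 18. The constant hazard ignores recovery, although scores may fall. Both points are fair, and the figures show only what unequal gaps could do.

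A reader might infer four stronger things that the documents do not support:

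- *That reassessment timing is known to differ by group.* No group-specific rates are given. Long-term home care clients share one annual schedule, and controls are described as entering such care at about the same time. Differential timing is plausible but not shown.
- *That 20% to 40% of outcomes are missing.* That remainder is only an upper bound on never reassessed. It includes people reassessed soon after 12 months, essentially on schedule, and people whose follow-up ended by death or admission. The percentages also describe people assessed in general, not the matched cohort.
- *That scores will be imputed for people who have died or entered a care home.* The plan does not say so, and follow-up ends at those events. The imputation sentence reads naturally as covering missing items or records; it just does not state that limit.
- *That the depression outcome has the same defect.* It is status at a cut point of 3 or higher, not change since the last assessment.

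**Conclusion.** The point holds for ADLh and CPS decline. The outcome is a risk over an interval that varies by the plan's own figures, and the stated model does not account for that interval. If intervals differ by exposure, this alone could create or hide an effect: OR 0.77 for 12 against 15 months, 0.62 for 12 against 18, and about 0.90 for a milder imbalance, all under an assumed equal constant hazard of 0.3 per year. The true size and direction cannot be determined from the document. The expectation of little missing data is also not reconciled with the reassessment figures for outcomes taken from the RAI-HC. The interval argument does not affect the depression, service-use or care home outcomes.

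**What to change.** 1. For ADLh and CPS decline, use a complementary log-log link with an offset for the log of time since the previous assessment. At the least, include that interval as a covariate. Define time of assessment explicitly.
2. Report the distribution of intervals and the proportion reassessed, by group and province.
3. Limit the expectation of little missing data, and multiple imputation of RAI-HC outcomes, to missing items within completed assessments. State that no RAI-HC outcome is imputed after death or care home admission.
4. Optionally, as sensitivity analyses, use only the assessment nearest 12 months (±3 months) after index, or weight by the inverse probability of being reassessed. The fixed window discards assessments outside 9 to 15 months, so neither needs to be primary.

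The cost is a few sentences and modest programming with assessment dates already in the data. It is best done before the shared programs go to the three provinces.
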